#### Administration of study medication

Participants randomized to the lower dose of LT4 (intervention) to achieve the desired target TSH level of 4.1 to 8.0 mU/L, are likely to have their LT4 medication reduced by 25 mcg once a day at visit 1.

LT4 will be provided as two separate 13-week supplies (dispensed separately at visits 1 and 2; see Table 1). The container will be labeled appropriately but will not indicate the arm of the study to which the participants have been randomized. The label will instead contain a pack number, which will be the link to the relevant packaged dose.

**Table 1 T1:** SORTED A study assessments

	**Pre-screening**	**Screening**	**Baseline**	**Follow-up**		
**Visit**			**1**	**2**	**3**	**4 (phone call only)**
**Assessments**^**a**^	**Within 3 months of baseline visit**	**Week −4 to −1**	**Day 0**	**Week 12 (+/− 7 days)**	**Week 24 (+/− 7 days)**	**Week 25 (+/− 3 days)**
Identification and initial approach (including provision of PIS)	X					
Eligibility criteria checked (as per routine clinical practice)	X					
Written informed consent (including discussion of study in detail, questions answered)		X				
Physical examination (height,^e^ weight, blood pressure, pulse)			X		X	
Venepuncture			X^b^	X^c^	X^d^	
Clinical history (relevant medical history, medication list/history)			X			
Participant-completed questionnaires (ThyDQoL, ThySRQ, EQ-5D)			X		X	
Nurse-administered questionnaires (FRAT, TUG)			X		X	
Randomization (after all eligibility criteria checked and written informed consent obtained)			X			
Study medication prescribed and dispensed (following LT4 dose assessment at visit 2 only)			X	X		
Study medication compliance checks				X	X	
Concomitant medication			X	X	X	
Adverse events				X	X	
Serious adverse events				X	X	X

^a^ Study-specific procedures must only be performed once written informed consent is obtained from the participant; ^b^ 10 ml blood: TSH, FT4, FT3, thyroid peroxidase antibodies, total cholesterol, HDL, triglycerides, serum CTX; ^c^ 5 ml blood: TSH, FT4, FT3 only; ^d^ 10 ml blood: TSH, FT4, FT3, total cholesterol, HDL, triglycerides, serum CTX; ^e^ height to be measured at the baseline visit only.

FT3: free triiodothyronine (thyroid hormone); FT4: free thyroxine; HDL: high-density lipoprotein; serum CTX: serum collagen type-1 cross-linked C-telopeptide; TSH: thyroid stimulating hormone, PIS: participant information sheet.

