The study medication will be prescribed by an authorized study physician according to the protocol, using a trial specific prescription (documenting the required IMP dose), and dispensed according to local pharmacy practice. The relevant pharmacy will hold a corresponding list allowing pharmacy staff to correlate IMP pack number with the relevant packaged IMP dose for any particular IMP bottle, thus maintaining the single blind.

To further maintain the single blind, the research team at each site will deliver the trial prescription to the pharmacy and collect the relevant study medication to provide to the patient. Participants will be advised to take the IMP capsule orally once a day as usual. This will be discussed at the time of consent and will be clear in the patient information sheet.

Participants will be informed of potential adverse reactions and advised to contact the relevant study team as required. A study-specific participant contact card will also be provided.

Once randomized, participants will begin their study medication on Day 0 (Table 1).

At 12 weeks (+/− 7 days), serum TSH levels will be checked and the LT4 dose adjusted as follows (the second bottle of IMP should be started at week 12 (+/− 7 days)):

Control (usual) dose arm, TSH level:

≤0.39 mU/L: LT4 reduced by 25 mcg once daily

0.4 to 4.0 mU/L: Stay on current dose of LT4

≥4.1 mU/L: LT4 increased by 25 mcg once daily

Lower dose arm, TSH level:

<0.4 to 4.0 mU/L: LT4 reduced by 25 mcg once daily

4.1 to 8.0 mU/L: Stay on current dose of LT4

>8.1 mU/L: LT4 increased by 25 mcg once daily

The LT4 treatment based on the above regimen will continue for a total of 24 weeks at which point the final set of study-specific assessments will be made (with a further follow-up phone call at 25 weeks). If, during the course of the study, individuals on 25 mcg/day of LT4 require a reduction in their dose of LT4, their LT4 dose will remain unchanged as otherwise they would need to discontinue LT4 therapy completely.

At visit 3, participants on each arm of the study will stop their IMP and will be referred back to their GP, who will promptly prescribe the LT4 dose they were taking prior to study participation. The GP letter (sent once the participant is randomized) and the GP follow-up letter (sent after each participant completes his/her IMP) instruct the GP to check TSH levels for each participant, three months after he/she has completed his/her IMP.

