At the end of visits 2 and 3, participants will be asked to return any surplus study drug in the original packaging to the study team, who will verify and document compliance. All unused study medication and packaging will be sent to the local pharmacy for documentation and destruction as per local policy (following appropriate reconciliation by the trial manager).

Documentation of prescribing, dispensing and return of study medication will be maintained for study records.

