#### Primary outcome measures

• Participants’ willingness to enter the trial (ratio between those who consented to participate and those who were eligible and approached)

• Participants’ acceptability of study design (as measured by the completion rate of participants in each randomized group).

• Participant recruitment rate (as measured by the number of patients randomized divided by the length of the recruitment period) – the recruitment period runs from the date that recruitment opened to the date of the last randomization.

• Dose titration strategy, described above, and length of time required to achieve desired TSH levels (number of participants in each group that reach target TSH range at both 12 and 24 weeks)

• Medication compliance (tablet count).

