#### Study compliance and withdrawal

Compliance with study medication (IMP) will be assessed and documented by the research team by checking and recording the number of return capsules at each visit. This allows any issues to be addressed immediately with the participant. Compliance will be classed as good if between 80% and 100%.

Participants may withdraw from the study at any time without giving a reason. The investigator may also withdraw patients from the study drug in the event of inter-current illness, adverse events, serious adverse events, suspected unexpected serious adverse reactions, protocol violations or administrative or other reasons. Participants who withdraw will be asked if they would be willing to provide follow-up data collected as per the study protocol. Participants withdrawn from the study will not be replaced.

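### The 13-week second bottle can run out 1 to 7 days before the 24-week sample if bottle 2 is started early and visit 3 falls late, both within their windows

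*Protocol article*

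**What the plan says.** All statements are in the Protocol article, SORTED A. Unless noted, they are under Administration of study medication.

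- Supply: "LT4 will be provided as two separate 13-week supplies (dispensed separately at visits 1 and 2; see Table 1".
- Dosing: "Participants will be advised to take the IMP capsule orally once a day as usual".
- Handover: "the second bottle of IMP should be started at week 12 (+/− 7 days".
- Leftovers: "At the end of visits 2 and 3, participants will be asked to return any surplus study drug in the original packaging".
- Duration: "The LT4 treatment based on the above regimen will continue for a total of 24 weeks".
- End of study drug: "At visit 3, participants on each arm of the study will stop their IMP". Table 1 places visit 3 at week 24 with a tolerance of 7 days either way, counted from Day 0 and not from visit 2. It shows dispensing at visits 1 and 2 only.
- Use of the last sample (Primary outcome measures): "number of participants in each group that reach target TSH range at both 12 and 24 weeks".
- Compliance class (Study compliance and withdrawal): "Compliance will be classed as good if between 80% and 100" per cent.

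**The concern.** A 13-week pack for a nominal 12-week interval holds one spare week. That absorbs one 7-day window. The interval between starting bottle 2 and visit 3 is bounded by two separate windows, which together can lengthen it by 14 days. The article does not tie the visit 3 date to the bottle 2 start, describes no top-up, and has the bottle 1 surplus handed back at visit 2.

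Someone who follows the schedule exactly can therefore be without levothyroxine in the last days before the visit 3 blood draw (TSH, FT4, FT3, lipids, CTX). That TSH value feeds the 24-week part of a primary outcome. Those who can run out are the most adherent participants, all aged 80 or over. The same section takes care elsewhere that nobody has to stop replacement, since participants on 25 mcg are not reduced further.

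**Working it through.** **Inputs**

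- Capsules in bottle 2: 13 × 7 = 91. The count is not printed; it assumes no overage.
- Bottle 2 start: 84 ± 7 = day 77 to 91.
- Visit 3: 168 ± 7 = day 161 to 175.
- The visit 3 day's own dose is not counted as needed.

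**Nominal timing.** 168 − 84 = 84 capsules needed, so 91 − 84 = 7 spare. The pack size works as intended.

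**Planned 24 weeks.** The earliest bottle 2 start is day 77, and 77 + 91 = day 168. Planned treatment is always covered. Bottle 1 (91 capsules from day 0) lasts through day 90, so it also covers any bottle 2 start up to day 91.

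**Longest interval.** 175 − 77 = 98 days; 98 − 91 = 7 capsules short.

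**When a gap occurs.** Shortfall = (visit 3 day − bottle 2 start day) − 91, which is positive when the interval is 92 days or more. That requires a start on day 77 to 83 and visit 3 on day 169 to 175. These ranges are necessary but not sufficient: start 77 with visit 169 is 1 day short, while start 83 with visit 169 has 5 days spare.

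**How many day pairs.** There are 15 × 15 = 225 permitted pairs. Shortfalls of 1, 2, …, 7 days occur in 7, 6, 5, 4, 3, 2 and 1 pairs, a total of 28, or 28/225 = 12.4%. The mean gap among these is 84/28 = 3.0 days. Counting the visit-day dose as needed gives 36 pairs and gaps of 1 to 8 days.

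**Adherence and handover lag.** With adherence a, a gap needs a × interval > 91. Even at 98 days this requires a > 91/98 = 92.9%. If bottle 2 starts d days after visit 2, with bottle 1 continued meanwhile and the start no later than day 91, the pairs running short out of 225 are:

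| Lag d | a = 100% | a = 97% | a = 95% |
|---|---|---|---|
| 0 days | 28 (12.4%) | 15 (6.7%) | 6 (2.7%) |
| 1 day | 21 (9.3%) | 10 (4.4%) | 3 (1.3%) |
| 3 days | 10 (4.4%) | 3 (1.3%) | 0 |
| 7 days | 0 | 0 | 0 |

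**Tighter visit keeping (d = 0, a = 100%).** Within ± 5 days, 6/121 = 5.0%; within ± 3 days, 0/49.

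**In participants, if all 50 reach visit 3.** 50 × 28/225 = 6.2 in the extreme case. For a lag of 1 to 3 days and 95% to 97% adherence, the range is 0 to 50 × 10/225 = 2.2.

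**Compliance class.** 91 capsules over 98 days is 92.9%, still good.

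**The case against.** The strongest objection is that bottle 2 is unlikely to start on the day of visit 2. Its dose depends on the TSH drawn at that visit, Table 1 places dispensing after the dose assessment, and the team must take a prescription to the pharmacy and bring the bottle back, sometimes for a participant seen at home. Some lag is therefore likely, and during it the participant presumably continues bottle 1. This stands. It is why the 12.4% is the extreme case and the lagged figures are the realistic ones. It does not remove the problem, because the text itself allows a bottle 2 start from day 77.

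Second, an article leaves pack counts, overage, booking rules and resupply to the full protocol or a pharmacy manual. That is fair, and a cap or overage may exist there. But the point rests on what is printed: pack size, both windows and the return rule do not fit together at the edges. The surplus stock mentioned under Study medication concerns production runs per dose, not extra capsules per participant.

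Third, the two bottles hold 182 capsules, more than the 175-day maximum. That helps only if bottle 1 is kept. It is to be returned at visit 2, and its strength would be wrong after a dose change.

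A reader might also infer that planned treatment is under-supplied, that about one participant in eight will run out, or that the 24-week TSH outcome is biased. The documents support none of these. Supply always reaches day 168, the one-in-eight figure needs zero lag, perfect adherence and evenly used windows, and nothing in the article allows the effect of a few missed days on TSH classification to be quantified.

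**Conclusion.** The point holds as a minor design flaw that is cheap to remove. Bottle 2 does not cover every timing the windows permit: an interval of 92 to 98 days leaves a near-fully adherent participant 1 to 7 days short before the final sample.

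The realistic size is 0 to 4.4% of day pairs, or about 0 to 2 of 50 participants. This rests on visits spread evenly and independently over the windows, a handover lag of 1 to 3 days, 95% to 97% adherence and exactly 91 capsules in the bottle. The actual pattern of visit dates is unknown; visits kept within ± 3 days give no shortfall.

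The effect on the 24-week count in target range is probably small. It would matter only for TSH values close to a range limit, in a feasibility study whose analysis is largely descriptive. The reason to act is to avoid an unplanned treatment gap, and to avoid carrying the mismatch into SORTED II.

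**What to change.** Add one scheduling rule: visit 3 takes place within its window and no later than 91 days after bottle 2 is started, with that start date recorded. The latest visit 3 day becomes the smaller of 175 and start + 91.

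This has no supply cost. Its price is a narrower visit 3 window, and only when bottle 2 starts before day 84. At the extreme, a start on day 77, the window is day 161 to 168 (8 days instead of 15). From day 84 onward, 84 + 91 = 175 and nothing changes.

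Alternatively, make the second pack a 14-week supply (98 capsules), which covers the longest permitted interval. That costs 7 extra capsules per participant, 7 × 50 = 350 in all, and slightly more surplus to reconcile and destroy.

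If the dose on the day of visit 3 is also to come from bottle 2, use 90 days for the cap or 99 capsules for the pack.

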#### Primary outcome measures

• Participants’ willingness to enter the trial (ratio between those who consented to participate and those who were eligible and approached)

• Participants’ acceptability of study design (as measured by the completion rate of participants in each randomized group).

• Participant recruitment rate (as measured by the number of patients randomized divided by the length of the recruitment period) – the recruitment period runs from the date that recruitment opened to the date of the last randomization.

• Dose titration strategy, described above, and length of time required to achieve desired TSH levels (number of participants in each group that reach target TSH range at both 12 and 24 weeks)

• Medication compliance (tablet count).

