**Methods/design:**

SORTED is a mixed methods study with three components:

SORTED A: A feasibility study of a dual-center single-blinded randomized controlled trial of elderly hypothyroid patients currently treated with levothyroxine.

Setting: Patients will be recruited from 20 general practices and two hospital trust endocrine units in Northumberland, Tyne and Wear.

Participants: Target recruitment of 50 elderly hypothyroid patients currently treated with levothyroxine, identified in both primary and secondary care settings.

Intervention: Reduced dose of levothyroxine to achieve an elevated serum thyroid stimulating hormone (target range 4.1 to 8.0 mU/L) versus standard levothyroxine replacement (target range 0.4 to 4.0 mU/L).

Randomization: Using random permuted blocks, in a ratio of 1:1, randomization will be carried out by Newcastle Clinical Trials Unit.

Outcomes: Study feasibility (recruitment and retention rates and medication compliance), acceptability of the trial design, assessment of mobility and falls risk, and change in cardiovascular risk factors.

SORTED B: Qualitative study using in-depth interviews to understand patients’ willingness to take part in a randomized controlled trial and participants’ experience of the intervention.

SORTED C: Retrospective cohort study of 400 treated hypothyroid patients aged 80 years or over registered in 2008 in primary care practices, studying their 4-year cardiovascular outcomes to inform the power of SORTED II.

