#### Primary objectives

The primary objectives are to show that recruitment to such a trial is possible; to gauge participants’ acceptability of being part of the study; to assess the length of time required to complete recruitment; to assess the dose titration strategy and the length of time required to achieve desired TSH levels; and to gauge medication compliance.

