#### Sample size calculation

No formal sample size calculation has been performed for the RCT component of this feasibility study as the primary outcome measures are concerned with the recruitment to and randomization of the trial and the acceptability of the trial in this population of patients. As this is a trial with 6 months follow-up, any investigation of changes in key study parameters from baseline to 6 months will only be exploratory. A sample size of *n* = 50 will provide sufficient data [14] to estimate the variability in the responses at baseline and assess the feasibility of the trial.

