## Trial status

The study received NHS ethics approval (REC Reference: 12/NE/0098) on 3 April 2012, NHS Trust governance approvals on 25 July 2012 and recruitment commenced on 15 October 2012. Recruitment will proceed until 31 July 2013. Results will be submitted for publication in 2014.

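### The primary recruitment rate stops its clock at the last randomisation, so an empty period at the end of recruitment would be left out and the rate overstated

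*Protocol article*

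**What the plan says.** The Protocol article, SORTED A, Primary outcome measures, lists "Participant recruitment rate (as measured by the number of patients randomized divided by the length of the recruitment period" and then fixes the denominator: "the recruitment period runs from the date that recruitment opened to the date of the last randomization".

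The Trial status section gives the calendar: "recruitment commenced on 15 October 2012. Recruitment will proceed until 31 July 2013". The abstract's Methods/design section gives the aim: "Target recruitment of 50 elderly hypothyroid patients currently treated with levothyroxine". No section says that recruitment closes once the 50th participant is randomised, and no second rate covering the whole open period is defined.

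The rate serves the Primary objectives, which include showing that recruitment is possible and "to assess the length of time required to complete recruitment". The Sample size calculation section states that "No formal sample size calculation has been performed for the RCT component of this feasibility study", and the Statistical analysis section makes the analysis mainly descriptive.

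**The concern.** Days on which the study is open and nobody is randomised are exposure with zero events, and a rate should count them. This definition counts them if someone is randomised later, but drops them if nobody is. The end of the denominator is therefore set by the outcome being measured, and an empty final stretch can only push the rate up.

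Such a stretch is plausible. The general-practice stream works from database searches, with packs posted soon afterwards and a reminder after 4 weeks without a reply, so it draws on finite lists that could run out before the closing date. The article does not say when the searches are run, and the clinic and poster routes could continue, so this shows only that a gap could occur.

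At stake is whether a feasibility outcome can look adequate when recruitment has in fact dried up short of target.

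**Working it through.** The article states no recruitment-rate figure, so there is none to reproduce. The check is date arithmetic on the definition.

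**Inputs from the article**
- Opening 15 October 2012 and planned closing 31 July 2013 (Trial status): T = 289 days, and 289/30.4375 = 9.49 months.
- Target 50 (abstract). Rate needed to reach it in the window: 50/9.49 = 5.27 per month.

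**Inputs not in the article, taken as assumptions**
- Gap g from last randomisation to closing: 0 to 90 days.
- Number randomised n: 20 to 50.

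**Formulas**
- Rate as defined: n/(T − g).
- Rate over the open period: n/T.
- Ratio of the two: T/(T − g), whatever n is.

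| Assumed gap g (days) | T − g (days) | Overstatement T/(T − g) |
|---|---|---|
| 0 | 289 | 1.00 |
| 30 | 259 | 1.12 |
| 60 | 229 | 1.26 |
| 90 | 199 | 1.45 |

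**Worked cases (assumed)**
- n = 40, g = 60. As defined: 40/(229/30.4375) = 5.32 per month, just above the 5.27 needed. Over the open period: 40/9.49 = 4.21 per month. Projected time to 50 is 50 × 229/40 = 286 days against 50 × 289/40 = 361 days. A study ten short of target would report a rate that looks on target.
- n = 30, g = 90. As defined: 30/(199/30.4375) = 4.59 per month. Over the open period: 30/9.49 = 3.16 per month.

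**No stall, constant rate, calendar closing.** Even here the last randomisation usually falls a little before closing. In a simulation of Poisson recruitment (40,000 runs at each level), the rate as defined averaged 1.02, 1.03 and 1.05 times the true rate with 50, 30 and 20 expected. So the ordinary effect is about 2 to 5%, and anything larger needs a real gap at the end.

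**Closing at the 50th randomisation.** The two denominators are then the same. An average upward bias of about 2% remains (50/49 = 1.02), as with any rate stopped at a fixed count.

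**Timing of randomisation.** Table 1 places screening and consent 1 to 4 weeks before randomisation on Day 0. If 31 July is the last day for consent, randomisation could run 28 days further, to 28 August, giving 289 + 28 = 317 days. Stopping the clock at 31 July while counting those late participants would overstate the rate by up to 317/289 = 1.10. The corrected end date must therefore refer to closure to randomisation.

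**The case against.** The strongest defence is that the definition is explicit and reproducible, and the opening and planned closing dates are published, so a reader given the number randomised can work out the full-window rate. The analysis is descriptive and no progression threshold is tied to the rate. Ending at the last randomisation also suits the objective about time to complete recruitment when the target is met. The start-up weeks, when hardly anyone can yet be randomised, are in the denominator and pull the rate down. Sampling error is wide as well: an exact Poisson 95% interval for 30 events is about 20.2 to 42.8, or 2.1 to 4.5 per month over 9.49 months.

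Much of this stands, and it limits both scope and grade. It does not rescue the definition. The declared primary outcome would still be the inflated figure. Wide sampling error does not excuse a one-directional error. The start-up weeks are genuine open time and do not offset a dropped tail by any known amount.

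Some stronger readings are tempting but not supported:
- That the rate is overstated whenever recruitment stalls. A stall followed by even one later randomisation is counted in full.
- That the bias disappears only if the target is met and recruitment closes that day. It also disappears if the last randomisation falls on the closing date, whatever the total.
- That this rate fixes the length or number of sites of SORTED II. The article lists recruitment rates among several things that will inform that trial and ties no such decision to this figure.

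**Conclusion.** The point holds in a conditional form. If the target of 50 is missed and the study stays open with no randomisations at the end, the rate as defined is too high by T/(T − g). With T = 289 days, that is about 12%, 26% or 45% for gaps of 30, 60 or 90 days. These gaps are assumptions. A reader might infer that an overstatement of this size will occur in this trial, but the document gives neither the gap nor the number randomised, and with steady recruitment the average effect is only about 2 to 5%. There is no material bias if the last randomisation falls at closing or the study closes at the 50th.

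It should be fixed, because the definition works when recruitment succeeds and can mislead when it dries up at the end. It is not a critical fault, since the rate is descriptive and carries no decision threshold.

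**What to change.** Redefine the end of the recruitment period in one sentence, for example: *the recruitment period runs from the opening date to the date the study closed to randomisation, which is the date of the 50th randomisation or the calendar closing date (including any time allowed for randomising patients who had already consented), whichever comes first.* Report the version ending at the last randomisation only as a supplement, labelled as such. State whether 31 July 2013 is the last date for consent or for randomisation.

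A confidence interval for the rate fits the existing plan to give 95% intervals where appropriate. A rate per open site-month would be a useful extra. Neither is needed for the correction.

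The cost is one sentence and no new data, and it should be settled before results are reported. The downside is that the reported rate may be less favourable.

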#### Design

This is a feasibility study for a dual-center single-blinded RCT of elderly hypothyroid patients currently treated with LT4. It is a clinical trial of an investigational medicinal product. The study will compare the standard dose of LT4 (target TSH level 0.4 to 4.0 mU/L) with a lower dose of LT4 (target TSH levels 4.1 to 8.0 mU/L), until TSH is within the desired range. Post randomization, individuals will be assessed at 12 weeks (and LT4 dose adjusted) and at 24 weeks, with a final follow-up phone call at 25 weeks.

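### The primary titration outcome, read literally, leaves out participants brought into range by the week-12 adjustment; it also has a second reading, and neither reading gives time to target per participant

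*Protocol article*

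**What the plan says.** Under Primary objectives, SORTED A sets out "to assess the dose titration strategy and the length of time required to achieve desired TSH levels". Under Primary outcome measures, the matching item is headed "Dose titration strategy, described above, and length of time required to achieve desired TSH levels", and the quantity given for it is the "number of participants in each group that reach target TSH range at both 12 and 24 weeks".

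The strategy is described under Design and under Administration of study medication. A dose is set at day 0. The Design section then says: "Post randomization, individuals will be assessed at 12 weeks (and LT4 dose adjusted) and at 24 weeks". At week 12, "serum TSH levels will be checked and the LT4 dose adjusted as follows". In the lower-dose arm the rule for a TSH still below target is "<0.4 to 4.0 mU/L: LT4 reduced by 25 mcg once daily", and for a TSH in target it is "4.1 to 8.0 mU/L: Stay on current dose of LT4". A TSH above target leads to an increase. Someone on 25 mcg who would need a reduction is held: "their LT4 dose will remain unchanged as otherwise they would need to discontinue LT4 therapy completely".

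Table 1 schedules TSH at baseline, week 12 and week 24. The inclusion criteria require every TSH result in the three months before entry to lie between 0.4 and 4 mU/L. That is the control target range, and it lies below the lower-dose target of 4.1 to 8.0 mU/L.

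**The concern.** The follow-up schedule has one planned TSH-driven adjustment, at week 12, and its effect can first be seen at week 24. A participant who is off target at week 12, is adjusted, and is on target at week 24 is the person for whom the adjustment worked. A count that requires target TSH at both visits cannot include that person. It therefore gives no credit to the step under assessment.

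The wording can also be taken as a count at week 12 and another at week 24. The article does not say which is meant. Two analysts could report different values of a primary outcome from one dataset, each faithful to the text.

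The item also names a length of time, but what it defines is a count. At stake is whether the feasibility study can tell the designers of SORTED II how many people the scheme brought to target, and by when.

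**Working it through.** **No figure to reproduce.** The Sample size calculation section states that no formal calculation was done for the RCT, and the documents give no expected in-range rates. The check is therefore of the definition, with an illustration on assumed rates.

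**Inputs from the documents.** 50 participants (Abstract) allocated 1:1 (Randomization), so about 25 per arm. Follow-up TSH at weeks 12 and 24 (Design, Table 1). One planned adjustment, at week 12.

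**Assumed inputs.**
- a = proportion in range at week 12: 0.2 to 0.6
- s = proportion of those still in range at week 24: 0.8 to 1.0
- c = proportion of those out of range at week 12 who are in range at week 24: 0.3 to 0.7

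**Formulas.**
- In range at both visits = a × s
- In range at week 24 = a × s + (1 − a) × c
- Difference = (1 − a) × c, which does not depend on s

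**One worked case: a = 0.4, s = 0.8, c = 0.5, n = 25.**
- Week 12: 25 × 0.4 = 10.0
- Both visits: 25 × 0.4 × 0.8 = 8.0 (32%; Wilson 95% CI for 8/25 is 17% to 52%)
- Week 24: 8.0 + 25 × 0.6 × 0.5 = 15.5 (62%)
- In range at week 24 but not counted by the literal definition: 15.5 − 8.0 = 7.5 (30 percentage points)

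**Range of the difference.**
- Smallest: a = 0.6, c = 0.3 gives 0.4 × 0.3 = 0.12, or 3 of 25
- Largest: a = 0.2, c = 0.7 gives 0.8 × 0.7 = 0.56, or 14 of 25
- Over the same grid the both-visits count runs from 4 (25 × 0.2 × 0.8) to 15 (25 × 0.6 × 1.0). The week-24 count runs from 10 (a = 0.2, s = 0.8, c = 0.3) to 22 (a = 0.6, s = 1.0, c = 0.7).

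**Does the per-visit reading supply time to target?** Take whole-number counts close to the worked case: 10 of 25 in range at week 12 and 16 of 25 at week 24. Let b be the number in range at both visits. The two counts alone allow b from 10 + 16 − 25 = 1 up to 10. Then:
- First in range at week 24 = 16 − b, anywhere from 6 to 15
- In range at neither visit = 25 − 10 − (16 − b) = b − 1, anywhere from 0 to 9
- In range at week 12 but out at week 24 = 10 − b, anywhere from 0 to 9

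So two separate counts leave open who first reached target at week 24, who lost it and who was never in it. The literal reading gives b alone and leaves all of these open too. With TSH measured only at weeks 0, 12 and 24, time to target can be known at best as one of three classes: first in range at week 12, first in range at week 24, or in range at neither visit. Classifying people this way needs the cross-table.

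**The control arm.** Controls enter inside their own target range by eligibility. For them an in-range count describes maintenance, and time to reach target has little meaning.

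**The case against.** The strongest reply is that the per-visit reading is the natural one. The count stands as the measure of a length of time, and counts at two visits speak to time better than a single joint count does. It also fits the Design section, which describes assessment at each of the two visits. On that reading people adjusted successfully appear in the week-24 count and there is no shortfall. Per-visit counts would also come close to the resolution that three TSH measurements allow, and the layout of tables is usually left to an SAP, which is not shown here.

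Much of this stands. The per-visit reading is plausible, so a reader who infers that the plan definitely scores such participants as failures goes too far. The article sets no success threshold or test for this item, and describes its analyses as mainly descriptive. What does not fall away is that the article fixes the wording of a primary outcome, and that the more literal sense of that wording works against the matching objective. The per-visit reading does not supply time to target either, as the working shows.

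A reader might also infer that this count decides whether SORTED II goes ahead. No section makes it a progression criterion; it is one of five primary measures. Likewise, the 25 mcg floor and the four dose strata might suggest that results must be tabulated by stratum. With 50 participants over two arms and four strata there would be about 6 per cell if evenly spread (50 / 8), so that is a reporting preference and not a defect in the outcome.

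**Conclusion.** The point holds as a defect of definition. The primary titration outcome has two readings that give different numbers. The literal one leaves out participants who come into range after the week-12 adjustment, and neither gives the stated time to target per participant.

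Under the literal reading the shortfall against week-24 attainment is (1 − a) × c: 12 to 56 percentage points, or 3 to 14 of 25 per arm, for a of 0.2 to 0.6 and c of 0.3 to 0.7. These rates are assumptions, and the size depends on the correction rate as much as on the week-12 rate. Under the per-visit reading the shortfall is nil and only the loss of the participant-level time information remains. No sample size figure is affected, and the data themselves are not compromised.

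**What to change.** Redefine the outcome, per arm and with 95% CI, as:
1. the proportion in target range at week 12;
2. separately, the proportion in target range at week 24;
3. the week-12 by week-24 cross-table, with the dose action taken at week 12 (reduced, unchanged, increased).

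From the cross-table, describe time to target in the lower-dose arm as first in range at week 12, first in range at week 24, or in range at neither visit. Keep the both-visits count only as an added measure, labelled sustained attainment. Describe the control arm as maintenance of target range.

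The cost is a change of wording and one extra table. TSH at all three visits and the prescribed doses are already recorded, and confidence intervals are already foreseen under Statistical analysis. The titration rules are untouched.
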